## Abstract

**Background:**

Early identification of persons at risk of sickness absence due to work-related stress is a crucial problem for society in general, and primary health care in particular. Tho date, no established method to do this exists. This project’s aim is to evaluate whether systematic early identification of work-related stress can prevent sickness absence. This paper presents the study design, procedure and outcome measurements, as well as allocation and baseline characteristics of the study population.

**Method/design:**

The study is a two-armed randomized controlled trial with follow-up at 3, 6 and 12 months. Non-sick-listed employed women and men, aged 18 to 64 years, who had mental and physical health complaints and sought care at primary health care centers (PHCC) were eligible to participate. At baseline work-related stress was measured by the Work Stress Questionnaire (WSQ), combined with feedback at consultation, at PHCC. The preventive intervention included early identification of work-related stress by the WSQ, GP training in the use of WSQ, GP feedback at consultation and finding suitable preventive measures. A process evaluation was used to explore how to facilitate future implementation and structural use of the WSQ at the PHCC. The primary outcome to compare the preventive sick leave intervention by the general practitioner (GP) versus treatment as usual is sick leave data obtained from the Swedish Social Insurance Agency register.

**Discussion:**

Early screening for sick leave due to work-related stress makes it possible not only to identify those at risk for sick leave, but also to put focus on the patient’s specific work-related stress problems, which can be helpful in finding suitable preventive measures. This study investigates if use of the WSQ by GPs at PHCCs, combined with feedback at consultation, prevents future sickness absence.

**Trial registration:**

ClinicalTrials.gov. Identifier: NCT02480855. Registered 20 May 2015

## Background

Work-related stress is common in many European countries, with Sweden representing the highest level of reported work stress in Europe [1, 2]. A number of organizational and psychosocial work-related factors are found to be associated with stress, which in turn might result in adverse health effects and illness, and a higher risk of sick leave. Work-related factors, such as poor organizational climate, in terms of intolerance at work [3, 4], conflicts [5, 6], and injustice at work [7] are associated with stress, poor health and subsequent sick leave. Being engaged in work or committed to work is basically considered to have a positive influence on both the individuals’ well-being and that of the organization [8, 9]. It has been demonstrated, though, that being too engaged, or over-committed, is a risk factor for sickness presenteeism [10], work-related stress [11] and poor health [12]. These organizational and psychosocial working life stressors and strains affect people negatively and result in various mental and physical health complaints, even prior to sick-listing [13–15]. People with these complaints often consult their primary health care physician [16–18] long before they even contemplate taking sick leave [11, 19]. It may well be that neither the patient, nor the general practitioner (GP) is aware that their symptoms could be caused by organizational and psychosocial factors at work. Because many patients might be at risk of disability and long-term sick leave, it is of immense value to identify these persons early and to take preventive actions [20].

Providing sickness certificates is a common task for GPs in Sweden [21, 22]. One third of Swedish GPs reported having 1–5 consultations each per week concerning sick leave [21]. This indicates that they often deal with assessing level of patients’ work incapacity in their everyday practice [21, 23]. GPs often found the decision about issuing a sickness certificate difficult, especially if the patients describe symptoms without clinical findings [21, 24]. Likewise, GPs stated that they had poor knowledge of the workplace environment and the labor market [23, 25], and they reported that they barely talked to patients about their work situation [26, 27]. Today, GPs have no established practice for early identification of patients at risk for sick leave caused by adverse psychosocial factors.

The Work Stress Questionnaire (WSQ) has been designed specifically for early identification of people at risk for sick leave due to work-related stress, and was developed in the context of primary health care [11, 19, 28]. The WSQ is based on the idea that personal characteristics and environmental factors are interdependent, and that changes in either of these influences the possibilities for a sustainable work performance [29–32]. Experiences from sick-listed people [11] contributed to the questionnaire development, and showed that a poor organizational climate, as exemplified by indistinct leadership and conflicts at work, in combination with high work commitment, such as excessive individual demands and responsibility, was crucial for future sick-listing [11]. A prospective Swedish primary health care study [19] found that high stress due to poor organizational climate at baseline, measured with the WSQ, more than doubled the risk for sick leave at follow-up. Combined with high stress due to high work commitment the risk for sick leave increased fourfold.

Early screening makes it possible not only to identify patients at risk for sick leave but also to identify the patient’s specific problems, which makes for the use of preventive measures and efficient treatment [33]. During the patient–GP consultation, tailored preventive measures for work-related stress can be suggested that might lower the risk of future sick leave. Since the WSQ takes both work-related factors and personal characteristics into account, it is possible to identify work-related stress from both an environmental and a personal perspective. Thus, the WSQ gives the GP the opportunity to direct preventive measures towards either the person or the workplace, or both. Therefore, it is important in GP practice to identify the patient’s specific problems at work early, to communicate them to the patient, and to recommend suitable preventive measures.

### Aims and hypothesis

The overall aim of this randomized controlled trial (RCT) is to evaluate whether systematic use of the WSQ, combined with feedback at consultation, can serve as a method for health care professionals in primary health care centers (PHCCs) to prevent or reduce sick leave due to work-related stress during a 12-month follow-up period. The preventive intervention will be compared versus treatment as usual (TAU). The aim is also to evaluate whether there are differences between the intervention group and the control group in healthcare measures and the prescribed medications at follow-up. In a process evaluation, the systematic use of the WSQ combined with feedback at consultation is examined.

The hypothesis of this RCT is that patients who answer the WSQ, when combined with feedback at GP consultation, will have fewer sick leave days during the year after intervention compared with those who receive TAU.

This paper presents the study design, the procedure, the outcome measurements, the allocation and the baseline characteristics of the study population. The project is still ongoing, with follow-up data to be collected and analyzes to be done. The RCT was designed in accordance with CONSORT recommendations [34].

## Method and design

### Study context

In Sweden, the social insurance scheme provides benefits to people who cannot work because of disease or injury. Those gainfully employed are covered for the first 14 days (except for one qualification day) by their employer, and after that period benefits are granted from the Social Insurance Agency. From day 8, a medical certificate is required. Providing sickness certificates is a common task for GPs in Sweden [21, 22]. This study is conducted in PHCCs in the Västra Götaland region with a population of 1.6 million inhabitants, around 17% of the Swedish population. The region has approximately 200 public and private PHCCs with approximately 800 employed GPs.

This RCT study is part of the TIDAS project within the New Ways research program at the Section for Epidemiology and Social Medicine, Institute of Medicine, Sahlgrenska Academy, University of Gothenburg.

### Study design and recruitment

This study was designed as a two-armed RCT for early identification of people at risk for sick leave due to work-related stress consulting PHCCs. The recruitment of PHCCs took place from May 2015 to November 2015. Out of the Västra Götaland region’s 200 PHCCs, 51 public and private PHCCs located in rural and urban areas in and around Gothenburg were identified and consecutively invited to participate. In all, seven PHCCs (four public and three private) participated. The PHCCs were economically compensated for each participant recruited.

### Randomization

GPs and residents who worked in the clinic at participating PHCCs at least 50% of the time were randomized to either the intervention or the control group. The names of all GPs at the participating PHCC were written on slips of paper that were folded and then mixed in a non-transparent bowl. Colleagues that were not involved in the RCT drew the names one at a time, and the names were alternately included in the intervention or the control group.

### Procedure

Prior to the intervention period, the research team visited the participating PHCC and presented the study procedure. The control GPs were instructed to carry on as usual with their consultations. The intervention GPs received a brief training for the intervention, which included knowledge on the relationship between psychosocial factors at work, stress, health and sickness absence. GPs also received instructions on how to use, operationalize and interpret the WSQ, and on how to give feedback to the participants and refer patients at risk. Both oral and written information on the services of the primary health care specialists and occupational healthcare was presented to the GPs.

### Masking (blinding)

Neither participants nor the GP were blinded to allocation in the RCT because of the nature of the intervention. All participants were given information on the study and signed consent forms before the patient–GP consultations. However, the control GPs were not informed when a patient for consultation was a study participant, and the controls filled in the questionnaires after consultation.

### Eligibility to participate

#### Inclusion criteria

Non-sick-listed employed women and men aged 18 to 64 years who saw a GP at the PHCCs in the Västra Götaland region for mental and/or physical health complaints, including depression, anxiety, musculoskeletal disorders, gastrointestinal, cardiovascular symptoms and other stress-related symptoms were invited [16–18].

#### Exclusion criteria

Patients seeking care for diabetes, urinary tract infections, infections, chronic obstructive lung disease, fractures, lump and spots, allergy and psychiatric diagnoses such as schizophrenia, other psychoses or bipolar diagnoses, as well as medical check-ups were excluded. Pregnant women were also excluded because they might be at risk for pregnancy-related sick leave during the follow-up period. Patients currently on sick leave and those who had been off work for a total of 7 days or more during the last month because of sickness, with or without medical record, were excluded, as well as those with a full or part-time disability pension.

### Sample size

A power calculation was performed to determine the number of participants needed to detect at least a 15% [35] difference between the intervention group and the control group concerning the primary outcome, i.e. the number of registered sick leave days (i.e. >14 days or more) during 12 months after inclusion. With a two-sided test, statistical significance of *p* < 0.05 and 80% power, at least 135 participants were needed in each group.

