#### Primary outcome

The number of registered sick leave days (i.e. 14 days or more) and number of absence periods during the 12 months after inclusion covered by sickness benefit will be obtained from the Swedish social insurance agency’s Micro Database for Analyzing Social insurance (MiDAS) as well as data on full- and part-time sick leave and sickness and activity compensation.

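### The stated 80% power at 135 per group for a 15% difference in sick leave days holds only if SD/mean is at most 0.44, which is not credible in this population

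*Protocol article*

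**What the plan says.** The Sample size section names the powered outcome as "the number of registered sick leave days (i.e. >14 days or more) during 12 months after inclusion". The target is "to detect at least a 15% [35] difference between the intervention group and the control group concerning the primary outcome", tested two-sided with "statistical significance of *p* < 0.05 and 80% power", and the result is at least 135 per group. It does not say whether the 15% is relative or absolute; it refers to a cited source for that figure.

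The other sections also describe an amount of absence. Under Primary outcome it is "The number of registered sick leave days (i.e. 14 days or more) and number of absence periods during the 12 months after inclusion". Under Aims and hypothesis, intervention patients "will have fewer sick leave days during the year after intervention compared with those who receive TAU". No section names the proportion of participants with any registered sick leave as the primary outcome. The Statistical analysis section reserves non-parametric methods for ordinal data and uses parametric methods otherwise, so a comparison of mean days is the natural reading.

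Three further statements bear on how the days will be distributed. The Inclusion criteria admit "Non-sick-listed employed women and men aged 18 to 64 years". The Exclusion criteria remove anyone with 7 or more days off in the last month. Absences under 14 days are a separate secondary outcome and do not count towards registered days.

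**The concern.** Most people who are working at entry can be expected to have no registered absence in the following year, and those who do will differ widely in its length. An outcome with many zeros has an SD that is large relative to its mean, and a 15% change in such a mean normally takes a very large trial to detect. A group size of 135 looks far too small for that purpose.

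What is at stake is how the result will be read. The Discussion counts reaching the target sample size among the study's good points. A reader who accepts 80% power for a 15% difference in days would take a non-significant result as fair evidence that no such difference exists. If true power is near 10%, it would be no such evidence.

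**Working it through.** **Inputs from the article:** two-sided 5%, 80% power, a 15% difference, 135 per group, outcome = number of registered days. **Assumed, because the article gives no value:** the share *p* with any registered day, and the CV *c* of days among those who have any. Observations are treated as independent.

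**Can 135 be reproduced?** Not from the stated inputs alone, because they fix no sample size without a variance or a control rate. The check therefore runs backwards: what must be true for 135 to be right?

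**Step 1. Required CV.** For a relative difference of 0.15 in means with equal SDs, n = 2 × (1.960 + 0.842)² × CV² / 0.15². Setting n = 135 gives CV = 0.15 / (2.802 × √(2/135)) = 0.15 / 0.341 = 0.44. If the CV rather than the SD is equal in both arms, the factor 2 becomes 1 + 0.85² = 1.7225 and the limit is 0.474.

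**Step 2. What the zeros imply.** If a share *p* has registered days with mean μ and CV *c*, and the rest have zero, the mean is pμ and the mean square is pμ²(1 + c²). Hence CV² = (1 + c²)/p − 1, which is never below 1/p − 1. A CV of 0.44 requires p ≥ 1/(1 + 0.44²) = 0.84 (0.82 with equal CVs). At that share every absentee would need the same number of days. With p = 0.84 and c as low as 0.5, power is already down to 42% (equal SDs).

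**Step 3. Results at 135 per group for a 15% relative reduction in mean days.** Power = Φ(d − 1.96) + Φ(−d − 1.96). With equal SDs d = 0.15 / (CV × √(2/135)); with equal CVs the 2 is replaced by 1.7225. *Detectable* is the relative reduction with 80% power at 135 per group.

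| p | c | overall CV | equal SDs: power; n per arm; detectable | equal CVs: power; n per arm; detectable |
|---|---|---|---|---|
| 20% | 0.5 | 2.29 | 8%; 3,663; 78% | 9%; 3,155; 60% |
| 20% | 1.0 | 3.00 | 7%; 6,280; none below 100% | 7%; 5,408; 75% |
| 30% | 0.5 | 1.78 | 11%; 2,210; 61% | 12%; 1,903; 48% |
| 30% | 1.0 | 2.38 | 8%; 3,954; 81% | 9%; 3,405; 62% |
| 50% | 0.5 | 1.22 | 17%; 1,047; 42% | 19%; 902; 35% |
| 50% | 1.0 | 1.73 | 11%; 2,094; 59% | 12%; 1,803; 47% |

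Worked line, p = 30%, c = 0.5, equal SDs: CV² = 1.25/0.3 − 1 = 3.167, CV = 1.78, d = 0.15 / (1.78 × 0.1217) = 0.69, power = Φ(−1.27) + Φ(−2.65) = 0.107. In the most favourable case at p = 30%, with no variation among absentees (c = 0), power is still only 13% and 1,628 per arm are needed.

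**Step 4. Other readings of the 15%.**
- *Log-ratio of means:* power is 27% at CV 1 and 10% at CV 2, much the same picture.
- *A 15% relative drop in a proportion:* 1,554 per group at a 30% control rate. It comes near 135 only at control rates between 85% (162 per group) and 90% (119).
- *A 15-percentage-point drop in a proportion:* 34% vs 19% gives 135; 30% vs 15% gives 121, or 134 with continuity correction; 50% vs 35% gives 170, or 183 with correction. Over control rates of 16% to 65% the uncorrected n runs from 54 to 174. It agrees with 135 only at roughly 30–36%, depending on the formula.

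**Step 5. Clustering.** GPs were randomised: 29 and 34 GPs for 271 patients, or 271/63 = 4.3 each. An assumed intracluster correlation of 0.01 to 0.05 gives a design effect of 1.03 to 1.17, so the power figures above are if anything slightly high.

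**The case against.** The article gives no mean, SD, control rate or test, and does not say whether the 15% is relative. Its inputs fix no sample size, so no printed calculation is shown to be wrong. A journal article may leave such inputs to the full protocol, and their absence is not a fault in itself. All of this stands. A reader might infer that 135 per group is impossible for days; the documents support only that it fails unless SD/mean is at most 0.44.

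A reader might also infer that the calculation was really made for a proportion, 30% vs 15%. The documents do not support that either. With the control rate free, some value will always give a number close to 135. The 30% vs 15% pair gives 121 unless a continuity correction that the article never mentions is added, and no section names a proportion as primary.

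The size of the shortfall depends on assumed values of *p* and *c* and on the variance model, which is why both models are shown. Recruitment is complete, so nothing in the design would change.

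What the objection does not remove is the claim as published. It names days and it names 80% power. The variance bound follows from algebra, and the zeros follow from the article's own entry criteria and outcome definition.

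**Conclusion.** The point holds in conditional form. For a 15% relative difference in mean registered days, 80% power at 135 per group requires SD/mean of at most 0.44 (equal SDs) and therefore at least about 84% of participants with registered sick leave of near-equal length. That is not credible for people at work at entry whose shorter absences are not counted.

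If 30% have registered absence with a CV among them of 0.5 to 1.0, power is about 8–11% with equal SDs (about 2,200 to 3,950 per arm needed) or 9–12% with equal CVs (about 1,900 to 3,400 per arm). Over assumed shares of 20% to 50% it stays below 20% under either model. These figures ignore clustering by GP.

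Confidence is high that the article does not support its power statement for days on this reading. How 135 was obtained remains unknown; a 15-point difference in a proportion is one possible origin among others.

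**What to change.** In the Sample size section, and in any full protocol or analysis plan that repeats it:

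- Withdraw the claim of 80% power for a 15% difference in number of days unless the original inputs support it.
- State the outcome the calculation used, whether the 15% is relative or in percentage points, the control rate or the mean and SD, and the test. If the outcome was binary, name it and say how it relates to the days outcome.
- Do not insert 30% vs 15%, or any other pair of rates, unless the original calculation confirms it.
- Report the difference in mean days detectable at 135 per group under stated assumptions, naming the variance model. For example, with p = 30% and c = 0.5 to 1.0 it is a 61–81% reduction with equal SDs or 48–62% with equal CVs, before clustering.
- State that a non-significant result for days will be interpreted by its confidence interval and not as evidence against a 15% effect.

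The cost is a text correction and retrieval of the original calculation. No extra patients are needed, and neither the outcome nor the analysis changes. The stated power for days will become much less favourable.

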**Fig. 2 Fig2:**
[figure not shown]
Flow chart of enrolment, allocation and baseline, TIDAS in New Ways

During the inclusion period, 301 non-sick-listed employed women and men aged 18 to 64 years who sought care at the seven participating PHCCs in the Västra Götaland region and fulfilled the inclusion criteria were asked to participate in the study. Of these, 20 eligible patients (7%) declined to participate. A total of 10 patients (3%) were excluded because they left the PHCC before being asked to fill in the questionnaires. No statistically significant differences in responses by participant age or gender were found. The final study population consisted of 271 participants (Fig. 2), of which 132 belonged to the intervention group and 139 to the control group.

The mean age was 46 years (standard deviation = 12) in the intervention group and 43 years (standard deviation = 11) in the control group, with a larger proportion in the age group 51–64 among intervention participants. Also, a larger proportion in the intervention group was consulting the PHCC for musculoskeletal reasons. Otherwise, there were no statistically significant differences between the groups in terms of baseline characteristics concerning sociodemographic factors and reasons for consulting the PHCC (Table 1).

**Table 1 Tab1:** Characteristics of participants in the intervention and control groups, *n* = 271, TIDAS in New Ways

	Intervention *n* = 132	Control *n* = 139
	n^a^ (%)	n^a^ (%)
Gender		
Female	88 (67)	97 (70)
Age categories		
19–30 years	21 (16)	26 (19)
31–50 years	58 (44)	76 (54)
51–64 years	53 (40)	37 (27)^c^
Birthplace		
Nordic countries	122 (93)	125 (90)
Other	9 (7)	14 (10)
Educational level		
Compulsory schooling	13 (10)	15 (11)
Secondary school	61 (46)	59 (42)
University or higher	57 (44)	65 (47)
Occupational class		
Skilled/unskilled manual	49 (37)	58 (42)
Medium/low non-manual	60 (46)	56 (41)
High-level non-manual	23 (17)	24 (17)
Employer		
Private	61 (46)	68 (49)
Public	66 (50)	61 (44)
Self-employed	5 (4)	9 (7)
Reason for consultation^b^		
Mental or behavioral	75 (57)	69 (50)
Musculoskeletal	62 (47)	44 (32)^c^
Gastrointestinal	26 (20)	28 (20)
Cardiovascular	16 (12)	16 (16)
Other	29 (22)	27 (19)

^a^Dispersed numbers of participants are owing to internal

missing data

^b^Multiple responses were optional

^c^Statistically significant differences (tested with the 95% CI for difference in proportion)

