Fortunately, we reached our target sample size for participating patients. Also, the fact that few sociodemographic differences were identified between the groups was an advantage. The intervention participants were somewhat older and had a higher rate of musculoskeletal complaints as reasons for consultation. The rates of patients declining and being excluded from participation were low, and no differences concerning gender and age were observed. A limitation is that we did not collect data on non-participation patients’ reasons for consultation or reasons to decline participation because of ethical considerations.

The advantages of randomizing at the GP level were considered as twofold: the risk for variations in sociodemographic and socioeconomic factors between participating patients in intervention and controls were reduced, and engaging the whole PHCC to recruit both to intervention and control groups led to more participants attending in earlier studies [44]. The disadvantage of randomizing at the GP level was the risk for contamination, because the GPs might discuss the study procedure with each other. Because the inclusion period was short, and the intervention was brief and imbedded in ordinary daily practice, the contamination risk was considered rather low.

A strength of this project is that both qualitative and quantitative methods were used in the process evaluation. The focus group methodology involves group discussions and is distinguished from other qualitative group interviews by the explicit use of group interaction to collect data on a specific research topic. Communication between the participating focus group members is decisive for the outcome and the group process encourages the participants to clarify not only what they think, but also how and why they think in a certain way [38, 45]. An experienced group leader was chosen to moderate the sessions because the role of the group leader is essential in creating an open and friendly atmosphere that makes participants feel free to express their views [45]. In addition to using the questionnaires on GPs’ readiness and feasibility in the process evaluation, they will be analyzed in relation to the outcome variables.

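### The stated 80% power shows no allowance for randomising GPs, and the target reported as reached was missed by three in the intervention group

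*Protocol article*

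**What the plan says.** The Sample size section plans "to detect at least a 15% [35] difference between the intervention group and the control group" in registered sick leave days over 12 months. It specifies a two-sided test with *p* "< 0.05 and 80% power", and concludes that "at least 135 participants were needed in each group". It gives no control-group rate, mean or standard deviation, does not say whether 15% is relative or in percentage points, and mentions no ICC, design effect or number of patients per GP.

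The Randomization section allocates GPs, not patients. Allocation and baseline characteristics reports 66 GPs randomised and, after three dropped out or were excluded, 29 in the intervention group and 34 in the control group. The 271 participants are described as those "of which 132 belonged to the intervention group and 139 to the control group".

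The Discussion returns to the design ("The advantages of randomizing at the GP level were considered as twofold") and weighs balance and recruitment against contamination. It does not mention the effect of clustering on precision. On recruitment it says: "Fortunately, we reached our target sample size for participating patients".

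**The concern.** Two separate statements are at issue.

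The first is the 80% power. Patients of the same GP share that GP's habits in certifying sick leave, so their outcomes may be correlated. A size worked out for independent patients then delivers less power than stated. Nothing in the Sample size section shows that this was taken into account, and the Discussion names only contamination as the drawback of allocating GPs. A null result would be read against a power that the design may not have.

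The second is the claim of a target reached. The criterion was set for each group, and one group is below it.

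**Working it through.** **Inputs from the article.** Two-sided alpha 0.05; power 80%; 135 per group; 132 and 139 recruited; 29 + 34 = 63 GPs. Mean patients per GP: m = 271/63 = 4.30. This takes all 63 GPs as having contributed patients; with fewer, m and the loss would be larger.

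**Assumed, because the article gives no value.** ICC 0.01, 0.05 and 0.10; CV of patients per GP either 0 (equal numbers) or 0.7.

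**Can 135 be reproduced?** Not from the stated inputs. Solving backwards:
- Two proportions 15 points apart, individually randomised, pooled two-sided test: 34% against 19% gives exactly 135 per group, and 35% against 20% gives 138. With a continuity correction, 30% against 15% gives 134.
- A 15% relative difference in mean days, n = 2 × (2.8016 × SD/mean ÷ 0.15)²: 135 requires SD/mean of about 0.44. A ratio of 1 needs 698 per group and a ratio of 2 needs 2,791.

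So 135 fits an unadjusted comparison of proportions, but the article does not say that this was the calculation.

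**Standardised effect, taking 135 as exact under independence.** (1.960 + 0.8416) × √(2/135) = 2.8016 × 0.1217 = 0.341.

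**Effect of 132/139 without clustering.** 0.341 ÷ √(1/132 + 1/139) = 0.341 ÷ 0.12153 = 2.806. Power = Φ(2.806 − 1.960) = 80.1%. The uneven split costs nothing.

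**With clustering.** Design effect DE = 1 + [(1 + CV²) × m − 1] × ICC; power = Φ(2.806/√DE − 1.960); size needed per group = 135 × DE, rounded up.

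| ICC | CV | DE | Power at 132/139 | Needed per group |
|---|---|---|---|---|
| 0.01 | 0 | 1.033 | 78.8% | 140 |
| 0.05 | 0 | 1.165 | 73.9% | 158 |
| 0.10 | 0 | 1.330 | 68.2% | 180 |
| 0.01 | 0.7 | 1.054 | 78.0% | 143 |
| 0.05 | 0.7 | 1.270 | 70.2% | 172 |
| 0.10 | 0.7 | 1.541 | 61.8% | 209 |

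Example, ICC 0.05 with equal numbers: DE = 1 + 3.30 × 0.05 = 1.165; 2.806/√1.165 = 2.599; Φ(0.639) = 73.9%. A t reference with 63 − 2 = 61 degrees of freedom lowers these powers by a further 1 to 1.5 points. Using proportions of 34% and 19% instead of means gives nearly the same values with equal numbers per GP (78.8%, 73.8% and 68.0%).

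**Target against recruitment.** Intervention 132 − 135 = −3; control 139 − 135 = +4; total 271 − 270 = +1.

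**The case against.** The Sample size section is a two-sentence summary in a journal article. It also omits the control rate or SD, so the calculation plainly used inputs that are not printed, and a clustering allowance could be among them. Other routes to 135 exist: 30% against 15% needs 121 per group unadjusted, and 121 becomes 135 with a design effect of about 1.12 (ICC about 0.035 at 4.3 patients per GP). Likewise 25% against 10% needs 100, which becomes 135 with a design effect of 1.35 (ICC about 0.11). This stands. The article shows no allowance, but it does not prove that none was made.

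The power figures above rest on a back-solved effect and on ICC and CV values that are not the article's. This also stands. At ICC 0.01 with equal numbers per GP the loss is only about one point; 62% needs both the highest ICC and the uneven cluster sizes.

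The sentence on the target does not say that it means each group, and both group sizes are openly reported. That is fair as to intent, but the article's only stated criterion is a minimum in each group, so the sentence does not agree with it.

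**Conclusion.** The point holds in a limited form. The 80% is unsupported as written. If 135 is unadjusted, which is the natural reading, power is overstated for any positive ICC, by roughly 1 to 12 points with equal numbers per GP and 2 to 18 points at a CV of 0.7, over the assumed ICC range of 0.01 to 0.10.

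A reader might infer that the 80% has been shown wrong by a known amount. It has not: 135 cannot be rebuilt from the article, and the ICC and CV are assumptions. A reader might also infer that falling three short in the intervention group contributes to the power problem. It does not, since 132 and 139 independent patients give 80.1%. The shortfall makes only the statement about the target inaccurate: it is true of the total and untrue of the intervention group.

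**What to change.** No further enrolment is called for.

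- **Sample size:** state the inputs behind 135 (control rate or SD, and whether 15% is relative or absolute) and whether a design effect was applied. If one was, give its ICC and cluster size. If none was, say that 135 assumes independent patients and report the power at 132/139 over an ICC range labelled as assumed; the table above shows the form.
- **Discussion:** replace the sentence on the target with: *271 recruited against 270 in total; 132 of 135 in the intervention group; target not adjusted for GP clustering.* Keep the last clause only if no design effect was applied.

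The cost is a text correction and, probably, a less favourable power figure. Recruitment and data collection are unaffected, and because the article describes follow-up as still ongoing, the correction can be made before the results are read.
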